** to be filled in after edits **

**A. SPECIFIC AIMS___________________________________________________________________________**

*List the broad, long-term objectives and the goal of the specific research proposed, e.g., to test a stated hypothesis, create a novel design, solve a specific problem, challenge an existing paradigm or clinical practice, address a critical barrier to progress in the field, or develop new technology.*

This study is a clinical trial investigating exposure of Mozart's Sonata for Two Pianos in D Major (hereafter K448) to a large cohort of pediatric and adult individuals with special needs, many of whom have epilepsy, who reside at the Thad E. Saleeby Center in Hartsville, SC. All individuals at the Thad E. Saleeby Center will participate in the study assuming completion of appropriate inclusion criteria, IRB approval from MUSC/MUHA and DDSN, and appropriate consent completion.

The specific aim of this study is to determine if exposure to K448 decreases seizure frequency in neurologically-impaired individuals. Detailed seizure-reporting is standard protocol at the Saleeby Center and therefore baseline data has been accumulated for the previous 4 years, making for long-term accumulation of pre- and post-exposure data analysis.

Secondary outcome measures will be collected, including (1) sleep patterns, (2) neurobehavioral dysfunction, and (3) other seizure characteristics. These outcome measures will be collected according to the standard recording procedures currently in place at the Saleeby Center, but will be extended to include all individuals.

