**D. RESEARCH DESIGN AND METHODS (including data analysis) __________________________________**

*Describe the research design and the procedures to be used to accomplish the specific aims of the project. Include how the data will be collected, analyzed, and interpreted and specify what statistical methods will be used. Describe any new methodology and its advantage over existing methodologies. Discuss the potential difficulties and limitations of the proposed procedures and alternative approaches to achieve the aims. As part of this section, provide a tentative sequence or time-table for the project. Point out any procedures, situations, or materials that may be hazardous to personnel and the precautions to be exercised.*

Study Subjects: Individuals at the Thad E. Saleeby Center are all candidates for participation in this study. The ages will range from 5 to 90 years old.

Inclusion criteria:

• Resident of the Thad E. Saleeby Center

• Epilepsy or seizure disorder

• At least one year of detailed seizure reporting prior to study starting date

Exclusion criteria:

• Severe hearing impairment

Written informed consent will be obtained for all participants. If an individual is not capable of giving informed consent, a parent or legal guardian will be asked to act in the best interest of the patient in accordance with DDSN Departmental Directive 535-07-PD (see consent form for more details).

Children and adults who have given informed consent to participate in this study will be randomized into two groups: Group 1 (2/3 of participants) will be exposed to Mozart music at night and Group 2 (1/3 of participants) will be exposed to silence at night. Special care will be taken to make sure the audio levels for Group 1 do not disrupt their sleep cycles. Preliminary data from a pilot study at MUSC shows that background music does not alter sleep patterns.

Group 1 Protocol: Exposure to K448 will occur nightly between the hours of 9:00 p.m. and 7:00 a.m. Each room will have a sound system installed in it to deliver the stimuli. The stimuli will be presented in the same pattern as the 2002 ten-subject pilot study at MUSC:

Pre-exposure: The first 9 minutes of each hour will be silent.

Exposure: 8.5 minutes of K448 will follow the silent baseline.

Post-exposure: 8.5 minutes of silence will follow K448 acting as a washout.

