**Targeted/Planned Enrollment Table**

Total Planned Enrollment Will contact [name] and [name] for these numbers…

| TARGETED/PLANNED ENROLLMENT: Number of Subjects | | | |
| --- | --- | --- | --- |
| **Ethnic Category** | Sex/Gender | | |
| Females | Males | Total |
| Hispanic or Latino |  |  |  |
| Not Hispanic or Latino |  |  |  |
| **Ethnic Category: Total of All Subjects*** |  | | |
| **Racial Categories** |  | | |
| American Indian/Alaska Native |  |  |  |
| Asian |  |  |  |
| Native Hawaiian or Other Pacific Islander |  |  |  |
| Black or African American |  |  |  |
| White |  |  |  |
| **Racial Categories: Total of All Subjects*** |  |  |  |

**The “Ethnic Category: Total of All Subjects” must be equal to the”Racial Categories: Total of All Subjects”.*

*- Identify the criteria for inclusion or exclusion of any subpopulation.*

*- Explain the rationale for the involvement of special classes of subjects, such as fetuses, neonates, pregnant women, children, prisoners, institutionalized individuals, or others who may be considered vulnerable populations. Note that 'prisoners' includes all subjects involuntarily incarcerated (for example, in detention centers) as well as subjects who become incarcerated after the study begins.*

*- If you propose to exclude any sex/gender or racial/ethnic group, include a compelling rationale for the proposed exclusion. For example, 1) the research question addressed is relevant to only one gender or 2) evidence from prior research strongly demonstrates no difference between genders.*

*- Provide either a description of the plans to include children or, if children will be excluded from the proposed research, then you must present an acceptable justification for the exclusion. For example, 1) the condition is rare in children as compared to adults or 2) insufficient data are available in adults to judge risk in children.*

*- List any collaborating sites where human subjects research will be performed, and describe the role of those sites in performing the proposed research.*

Thad E. Saleeby Center in Hartsville, South Carolina

b. Sources of Materials

*- Describe the research material obtained from living human subjects in the form of specimens, records, or data.*

*- Describe any data that will be recorded on the human subjects involved in the project.*

*- Describe the linkages to subjects, and indicate who will have access to subject identities.*

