**5(5):662-8.**

G. CONSULTANTS__________________________________________________________________________

*Where applicable, attach electronic versions of appropriate letters from all individuals confirming their roles in the project. Go to the application under “additional uploads” to attach this information*.

H. FACILITES AVAILABLE____________________________________________________________________

*Describe the facilities available for this project including laboratories, clinical resources, etc.*

The Thad E. Saleeby Center is a state-run facility operating under the South Carolina Department of Disabilities and Special Needs. The Saleeby Center is a permanent residence home for individuals with specials needs and disabilities who require assisted living. There are fifty-five 2-patient bedrooms divided among three wings of the facility. There are also 14 unique day rooms that are specifically designed for different tasks including reading, arts and crafts, physical therapy, etc. The Co-directors of the Saleeby Center stress a high level of care tailored specifically to each individual’s unique needs. There are currently 85-92 individuals residing at the Saleeby Center, most of whom have epilepsy or a seizure-related disorder and might benefit from this research study.

I. INVESTIGATOR BROCHURE ____________________________________________________

*If applicable, attach the electronic version of the investigator brochure. Go to the application under “additional uploads” to attach this information.*

J. APPENDIX_______________________________________________________________________________

*Attach any additional information pertinent to the application, such as surveys or questionnaires, diaries or logs, etc. Go to the application under “additional uploads” to attach this information.*

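### Allocation is set at 2:1 with no balancing on baseline seizure rate, although every entrant's rate can be known before the single start

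*Protocol*

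**What the plan says.** Section D of the protocol states that participants "will be randomized into two groups: Group 1 (2/3 of participants) will be exposed to Mozart music at night" and that "Group 2 (1/3 of participants) will be exposed to silence at night". No stratification, blocking, matching or other balancing factor is named, and no reason is given for the ratio.

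The information needed for balancing would exist before the start. One inclusion criterion in Section D is "At least one year of detailed seizure reporting prior to study starting date", and Section A reports that "baseline data has been accumulated for the previous 4 years". Sections D and E.5 give one tentative start date, and E.5 ends the study one calendar year later.

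On numbers, Section H says "There are currently 85-92 individuals residing at the Saleeby Center, most of whom have epilepsy or a seizure-related disorder" and "There are fifty-five 2-patient bedrooms divided among three wings of the facility". The enrolment table in Section E.1 is not filled in; it reads "Total Planned Enrollment Will contact" and then refers to people to be asked. Section D sets the age range at 5 to 90 years and names seizure frequency as the primary outcome, to be judged against earlier years. Section E.5 also plans a comparison with earlier years.

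**The concern.** Prior seizure rate is likely to be the strongest predictor of seizure rate during follow-up. The inclusion criteria set no minimum seizure count, so entrants may range from no recent seizures to very frequent ones. With a control arm of about 30 at most, randomisation without balancing can leave the arms visibly different on the very variable the trial measures.

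Such a difference weakens the precision of an unadjusted comparison and makes any result harder to defend, particularly in an unblinded trial at one centre. Balancing would be nearly free, because the participant list and the baseline records can be complete before allocation. Once the arms are allocated, no later analysis plan can rebalance them.

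**Working it through.** The protocol gives no sample size, power, effect size or variance, so there is no figure of its own to reproduce. The check asks how large the chance imbalance could be, and what it costs.

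**Inputs from the protocol**
- Ratio 2:1 (Section D).
- Census of 85 to 92 residents (Section H). At 2:1 this gives 57/28 or 61/31 if every resident entered, which is an upper bound.

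**Assumptions, not in the protocol**
- Log baseline seizure rate is normal with SD 1.0 to 1.5 between residents. A resident with no seizures has no log rate, so this is an approximation.
- N=60 (40/20) as a low case for those eligible and consenting.
- Residents are allocated singly, without restriction.

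**Step 1. Size of chance imbalance.** In SD units, the arm difference in mean log rate has standard deviation sqrt(1/n1 + 1/n2):
- N=85: sqrt(1/57 + 1/28) = 0.231
- N=92: sqrt(1/61 + 1/31) = 0.221
- N=60: sqrt(1/40 + 1/20) = 0.274

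**Step 2. Chance of a geometric-mean ratio above 1.5 in either direction.** This is 2 × [1 − Φ(ln 1.5 / (SD × value from step 1))], with ln 1.5 = 0.405. For N=85 and SD 1.0, 0.405/0.231 = 1.76, giving 7.9%. The table comes from 40,000 simulated allocations under the same model; the formula agrees within about 0.3 percentage points.

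| N (arms) | SD 1.0 | SD 1.5 |
|---|---|---|
| 92 (61/31) | 6.4% | 21.7% |
| 85 (57/28) | 7.9% | 24.0% |
| 60 (40/20) | 14.0% | 32.5% |

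**Step 3. Does the ratio cause this?** Hardly. At N=85 with 1:1 allocation the chances are 6.2% and 21.1%, against 7.9% and 24.0% at 2:1. The imbalance comes from not balancing on baseline.

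**Step 4. What remains if the analysis adjusts for baseline.** With a linear baseline covariate, chance imbalance inflates the variance of the treatment effect on average by 1.012 (N=85), 1.011 (N=92) and 1.018 (N=60). That is 1.1% to 1.8%, whatever the correlation between baseline and follow-up.

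**Step 5. What the adjustment itself gains.** The variance is multiplied by 1 − ρ², where ρ is the correlation between baseline and follow-up. For an assumed ρ of 0.5 this is 0.75, a 25% reduction; for 0.8 it is 0.36, a 64% reduction. Adjustment therefore matters far more than stratification.

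**Step 6. Cost of 2:1.** At fixed N the efficiency relative to 1:1 is 4 × (2/3) × (1/3) = 8/9. The standard error is sqrt(9/8) = 1.061 times as large. For an effect sized to give 80% power at 1:1 (two-sided 5%, assumed), power at 2:1 is 75.2%.

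**The case against.** The strongest reply is that Section D is silent and does not say that allocation will be simple. A balancing scheme may sit in an allocation plan or SAP that is not shown. This stands in part: the protocol cannot be read as ruling stratification out. But allocation is a design step taken before the first night of music, and the section that fixes the ratio is where the balancing factor belongs.

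A second reply is that baseline is not ignored, since Sections D and E.5 both plan a comparison with earlier years. This stands. A reader might infer that a few residents with very frequent seizures could decide the result. That presumes a raw comparison of follow-up counts, which the protocol does not plan. How baseline enters the model may properly be left to the SAP. If it enters as a covariate, little is left to gain from stratifying (step 4).

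Third, chance imbalance under randomisation is not bias, because the standard error already allows for it. This stands in full.

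Fourth, 85 to 92 is the centre's census and not a planned N. The epilepsy, record, hearing and consent conditions reduce it. Nor is it a strict cap, since fifty-five rooms for two could hold 110. This stands, which is why 28 to 31 controls is stated as a maximum and N=60 is shown.

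Finally, a reader might infer that the unexplained 2:1 split is an error that should be replaced by 1:1. The documents do not support that. Unequal allocation is a legitimate choice, its cost is modest, and it barely affects balance.

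**Conclusion.** The point holds as a missed and nearly free design improvement, not as a flaw that invalidates the trial. Baseline seizure rates can be known for every entrant before the single start, yet the allocation text makes no use of them.

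Without balancing, a more than 1.5-fold difference between arms in geometric-mean baseline rate has a probability of about 6-8% to 22-24% at N=85-92, and 14% to 33% at N=60. The consequence is lost precision and credibility. It shrinks to about 1-2% of variance if the primary comparison adjusts for baseline.

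These figures rest on the assumed log-rate SD of 1.0 to 1.5, approximate normality, the assumed N=60 and allocation of single residents. If whole rooms are allocated, imbalance would be larger to the extent that roommates have similar seizure rates. The 6% increase in standard error from 2:1 may be noted as a trade-off.

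**What to change.** In Section D, state that allocation will be stratified or constrained on each participant's seizure rate over the 12 months before the start. Use few strata, for example below and above the median. Crossing several rate levels with the three wings would leave only a handful of controls per stratum, and nothing in the protocol shows that wing predicts seizures.

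Name the allocation unit in the same place. Section D installs a sound system in each room and Section H describes rooms for two, so roommates cannot cleanly be in different arms. Where two participants share a room, the room should be allocated as one unit.

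State that the primary comparison of the randomised groups includes baseline seizure rate as a covariate, or point to the SAP if it already says so. One sentence giving the reason for 2:1 would also help; no change of ratio is required.

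The cost is slightly more work: extracting 12-month rates before allocation, and a somewhat more complex allocation list where roommates fall in different strata. No extra data collection is needed.

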The exposure and post-exposure epochs will play 3 times each hour before the cycle repeats the following hour beginning with another 9 minute baseline. Since the cycle is exactly 60 minutes in length, we will be able to deliver the entire stimulus train on one 80-minute compact disk from a central location in the Saleeby Center.

Group 2 Protocol: No music will be played for the control group. Evening and morning routines for both groups should remain identical.

Data Collection: A tentative start date for the project is January 1, 2006. Prior to this date, it is important to outline what data will be collected. The primary outcome measure for the study is seizure frequency. Therefore detailed records of seizure frequency by the Saleeby staff will be critical to quantifying any significant changes compared to baseline (previous years). Duration and intensity of seizures would also be useful as secondary measures of outcome in addition to sleep patterns and behavior.

Data will be collected on each individual for each outcome measure during the 12 month period of exposure. Interim analyses will occur monthly, quarterly, and at 6 months into the study.

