**E. PROTECTION OF HUMAN SUBJECTS________________________________________________________**

1. RISKS TO THE SUBJECTS

*a. Human Subjects Involvement and Characteristics*

*- Describe the proposed involvement of human subjects.*

*- Describe the characteristics of the subject population, including their anticipated number, age range and health status.*

The proposed involvement of human subjects is limited to the exposure of Mozart music to a subset of subjects while they are asleep. Everything else pertaining to the daily routine of each subject will remain unchanged. The subject population all have disabilities and special needs and are permanent residents of the Thad E. Saleeby Center. The age range is large (approximately 5 to 90 years old). Many of the individuals have epilepsy or a seizure disorder and would possibly benefit from this study.

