4. IMPORTANCE OF THE KNOWLEDGE TO BE GAINED

*- Discuss the importance of the knowledge gained or to be gained as a result of the proposed research.*

*- Discuss why the risks to subjects are reasonable in relation to the importance of the knowledge that reasonably may be expected to result.*

*- NOTE: Test articles (investigational new drugs, devices, or biologicals) including test articles that will be used for purposes or administered by routes that have not been approved for general use by the Food and Drug Administration (FDA) must be named. State whether the 30-day interval between submission of applicant certification to the FDA and its response has elapsed or has been waived and/or whether use of the test article has been withheld or restricted by the Food and Drug Administration, and/or the status of requests for an IND or IDE covering the proposed use of the test article in the research plan.*

The risk/benefit assessment for this project is excellent. The subjects are exposed to no more than minimal risk and the results, if valid, represent a significant non-invasive treatment for reducing seizure frequency, improving sleep patterns and reducing behavioral problems. Joining the research project is completely optional and if a subject joins and later decides to leave the study, they may do so without fear of penalty or loss of benefits.

5. SUBJECT SAFETY AND MINIMIZING RISKS (Data and Safety Monitoring Plan)

*Studies that involve *clinical trials (see description below) must include a description of the plan for subject safety and minimizing risks of the research, including data monitoring and adverse event reporting to ensure the safety of subjects. The complexity of the plan should be determined by the level of risk to subjects. The plan should specify: 1) what will be monitored, 2) how frequently the monitoring will occur, 3) who will be responsible for the monitoring, and 4) study endpoints.*

Data and safety monitoring will be the responsibility of the principle investigator ([name]) and the Co-directors of the Thad E. Saleeby Center ([name] and [name]).

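### K448 is delivered by two-bed room while consent, allocation and withdrawal are individual, and no rule keeps a roommate outside the trial from being exposed

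*Protocol*

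**What the plan says.** Delivery is by room. Under the Group 1 Protocol in section D, "Each room will have a sound system installed in it to deliver the stimuli", and the investigators expect to "deliver the entire stimulus train on one 80-minute compact disk from a central location in the Saleeby Center". Section H gives the layout: "There are fifty-five 2-patient bedrooms divided among three wings of the facility". On occupancy it says "There are currently 85-92 individuals residing at the Saleeby Center, most of whom have epilepsy or a seizure-related disorder".

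Everything else is set for the individual. Section D requires epilepsy or a seizure disorder, at least a year of detailed seizure records and no severe hearing impairment. It adds that "Written informed consent will be obtained for all participants" and that "Children and adults who have given informed consent to participate in this study will be randomized into two groups", two thirds of them to music. Section E.4 makes joining optional and adds that "if a subject joins and later decides to leave the study, they may do so without fear of penalty or loss of benefits".

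Section E.1.a sets the boundary of the research: "The proposed involvement of human subjects is limited to the exposure of Mozart music to a subset of subjects while they are asleep". It also says that the rest of each subject's daily routine stays as it was.

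The nearest safeguard is in section E.2.b, where the volume is to be set resident by resident. It is offered as protection against disturbed sleep. The protocol does not mention headphones, a roommate's consent, allocation by room, a check of who shares with whom, a change of room, or what happens in a shared room when one occupant leaves the study.

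**The concern.** A room sound system reaches both beds, but only one occupant may be in the trial. Some residents will be outside it: section H says most, not all, have epilepsy or a related disorder, and participation is optional. If such a resident shares with a Group 1 participant, that resident receives the study exposure nightly for the 12-month period without having agreed to it. A Group 1 resident who withdraws is in the same position if the roommate stays in Group 1.

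Section E.2.a says that most of these residents are unable to give informed consent, so the decision belongs to a guardian. A guardian who declined or withdrew would expect the exposure not to occur. There is a data consequence too: a resident recorded as withdrawn but still hearing the music has no correct date for the end of exposure.

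This differs from contamination of the silent arm. Group 2 residents who share with Group 1 would also hear K448, but placing participating roommates in the same arm would solve that. It does nothing when one occupant was never in the trial or has left it.

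**Working it through.** The protocol gives no figure of its own on this point, so there is none to reproduce. The check is a count of room occupancy.

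**Inputs from the protocol.** Residents N = 85 to 92 and rooms R = 55 with two beds each (section H). Group 1 share 2/3; music between 9 p.m. and 7 a.m. in hourly cycles with three 8.5-minute plays (section D).

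**Inputs assumed.** The share p of residents who take part (the enrolment table is blank), and pairing of roommates without regard to study status.

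**1. How many must share.** At least N − R rooms hold two people.
- N = 85: 85 − 55 = 30 rooms, 60 residents, 60/85 = 71%.
- N = 92: 92 − 55 = 37 rooms, 74 residents, 74/92 = 80%.

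At most 42 to 46 rooms are shared, which is practically everyone. At minimum sharing, 55 − 30 = 25 or 55 − 37 = 18 rooms are single.

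**2. Non-participants with a Group 1 roommate.** With S residents sharing (60 to 92), the approximate expected number is (1 − p) × S × p × 2/3.

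| p | S = 60 | S = 92 |
|---|---|---|
| 0.6 | 0.4 × 60 × 0.6 × 2/3 = 9.6 | 0.4 × 92 × 0.6 × 2/3 = 14.7 |
| 0.8 | 0.2 × 60 × 0.8 × 2/3 = 6.4 | 0.2 × 92 × 0.8 × 2/3 = 9.8 |
| 0.9 | 0.1 × 60 × 0.9 × 2/3 = 3.6 | 0.1 × 92 × 0.9 × 2/3 = 5.5 |

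A finite count, (non-participants) × (S/N) × (Group 1)/(N − 1), agrees:
- 80%, N = 85, S = 60: 17 × 60/85 × 45/84 = 6.4.
- 80%, N = 92, S = 92: 18 × 49/91 = 9.7.
- 90%: 9 × 60/85 × 51/84 = 3.9, up to 9 × 55/91 = 5.4.

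In simulation (4,000 draws per scenario) the chance of at least one exposed non-participant was 91% or more in every scenario from 50% to 95% participation.

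**3. Withdrawal.** No withdrawal rate is given, so no count is possible. Under individual allocation and the same pairing assumption, the chance that a given Group 1 resident shares with another Group 1 resident is (S/N) × (Group 1 − 1)/(N − 1). At 80% participation this runs from 60/85 × 44/84 = 0.37 to 48/91 = 0.53. For that share of Group 1, withdrawal alone would not end the exposure while the roommate remains.

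**4. Amount of exposure.** The cycle adds up: 9 + 3 × (8.5 + 8.5) = 60 minutes. Anyone in a Group 1 room is exposed to 3 × 8.5 × 10 = 255 minutes of music a night.

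**The case against.** A reader might infer that the plan as written does give the music to unconsented residents every night, and that its limits on exposure and its withdrawal promise cannot be kept. The document does not support that. It nowhere says that participants share with non-participants. Between 18 and 25 rooms could be single, and roommates could be grouped by status, so exposure is not forced by arithmetic. Nor does the text rule out managing rooms individually; per-resident volume even suggests some local control. The gap is a missing rule.

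A reader might also infer that harm in an exposed roommate would go unrecorded. That is not supported either. Section A extends outcome recording to all individuals, and section E.5 describes half-hourly night checks of each patient and behavioural records for each individual. What remains is narrower: the protocol does not bring the records of exposed non-participants into the trial's safety review.

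Three further objections have some force. The participation rates and random pairing are assumptions, and section A intends that all eligible, consenting residents take part. Residents excluded for severe hearing impairment count among the non-participants, though they may hear little, so the counts may overstate effective exposure. The intervention is quiet music that the protocol rates as minimal risk. This lowers the likely harm, but it does not replace the consent that the protocol itself makes a condition of taking part.

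Finally, section D refers to a consent form that is not available here. That does not answer the point, because a participant's form cannot consent on behalf of a roommate who is not in the trial.

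**Conclusion.** The concern holds in this form: delivery is by two-bed room, while eligibility, consent, allocation and withdrawal are individual, and no rule covers roommates of differing study status. The limit in section E.1.a and the free withdrawal in section E.4 are not secured as written.

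That at least 60 to 74 of the 85 to 92 residents share rests only on the protocol's figures. The expected numbers exposed, about 6 to 10 non-participants at 80% participation and 4 to 6 at 90%, rest on assumed participation and on pairing that ignores study status. Some exposure is very likely under those assumptions; deliberate grouping could reduce it to none. Because the residents are vulnerable and a year of exposure cannot be undone, this should be settled before the start. An analysis plan could not repair it.

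**What to change.** In section D, require a check of room occupancy before allocation, so that K448 is played only in rooms where every occupant, or the occupant's guardian, has consented to exposure. Allow a non-participating roommate to consent to exposure alone. Where that consent is not given, settle the room assignment before allocation or keep the room out of Group 1.

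Reconcile room-level delivery in section D with individual withdrawal in section E.4 and the unchanged daily routine in section E.1.a, so that the protocol says how a withdrawn resident's exposure in a shared room is handled. Record the date on which exposure ended. In section E.5, state whether the Center's records of non-participants who consent to exposure enter the trial's safety review.

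The cost is one consent line for roommates, one room check, and possibly a few rooms unavailable to Group 1.
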